#### Statistical analyses

2.4.4

All statistical procedures will be conducted with the IBM SPSS statistics software or R (RStudio, Boston, MA, United States). For demographics as well as training adherence and compliance, all collected data will be included (i.e., including data of dropouts up to the time point of their withdrawal). For all further analyses, only data of participants with an adherence ≥70% will be analyzed (per protocol analysis). A separate descriptive analysis of data from withdrawn participants who terminated the intervention prematurely or had to be excluded during the study or participants with adherence <70% will also be provided. Data will be reported as mean (SD) values for continuous parametric data and median (IQR) values for continuous nonparametric data. Data will be tested for normal distribution using Shapiro-Wilks Test and Q-Q-plots as well as for homogeneity of variance using Levene test. General level of significance used is established as *p* = 0.05. For the physical and cognitive tests that serve as secondary outcomes and are assessed in a pre-post manner, a two-way repeated measures ANOVA with group assignment (control vs. intervention group) as between subject factor and time-point (pre- vs. post-training) as within factor will be conducted. In case length of stay (and thus number of training sessions) vary across participants, we will conduct repeat our analyses controlling for this parameter. In order to determine the effects of the outcomes, effect sizes will be calculated for all primary and secondary outcomes. If any of the assumptions for parametric testing is not met, the non-parametric alternative (Friedman’s ANOVA) will be used. If the two-way mixed ANOVA or Friedman’s ANOVA report a significant group, time or interaction effect, data will be further analyzed using post-hoc tests. To calculate effect sizes of intragroup differences between post- and baseline measurements, a dependent T-test or its non-parametric equivalent (Wilcoxon signed rank test) will be used. The effect size will be interpreted using benchmarks describing the effect size as small (r ≥ 0.01), medium (r ≥ 0.3), or large (r ≥ 0.5) (56).

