The main challenge we anticipate is low recruitment rate. Inpatient clinics (at least in Switzerland) offer a wide variety of therapies which are offered in a very intensive manner; patients can have up to 1.5 h of therapy per day. This can lead to participation in the study be seen as a burden. Moreover, the study population (persons in the early-subacute phase) is extremely heterogeneous which can affect interpretation of the effect results. What is more, the study will take place in an inpatient rehabilitation clinic and thus training volume will not correspond to the current training recommendations for stroke patients. After a systematic review, healthy elderly people should perform exergame training two to three times per week for 45–60 min for 12 weeks and more to improve cognition (57). In addition, this study’s results will not be generalizable to other stages of the disease (e.g., chronic stroke) or settings (e.g., outpatient rehabilitation). However, examining the feasibility of this intervention within the scope of this study will give valuable information about whether or not such training can be integrated in the inpatient rehabilitation therapy plans. In addition, if found effective, this study would be the foundation for a larger study that is powered to detect effects. Most importantly, the information and knowledge gained from this project will help to adapt and further develop digital solutions and technologies to support patients, therapists, geriatric rehabilitation and potentially the whole health care system.

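### The pre-post ANOVA is valid for the between-arm question, but it forgoes baseline adjustment, and its post-hoc trigger and described effect sizes do not address that question

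*Protocol article*

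**What the plan says.** The efficacy hypothesis at the end of section 1 is comparative: labile training should improve motor and cognitive function more than stable training does. Section 2.4.4 sets out the analysis of the pre-post secondary outcomes:

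- The model is "a two-way repeated measures ANOVA with group assignment (control vs. intervention group) as between subject factor and time-point (pre- vs. post-training) as within factor".
- If the parametric or non-parametric ANOVA should "report a significant group, time or interaction effect, data will be further analyzed using post-hoc tests".
- The effect-size method described is within arms: "To calculate effect sizes of intragroup differences between post- and baseline measurements, a dependent T-test" (the Wilcoxon test where that is unsuitable), with r of 0.5 or more called large.
- The only adjustment variable is length of stay: "In case length of stay (and thus number of training sessions) vary across participants, we will conduct repeat our analyses controlling for this parameter".

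The same section promises effect sizes for every primary and secondary outcome, and means with SDs, but describes no between-arm effect-size calculation. It does not say which of the three ANOVA effects tests the hypothesis. Under section 2.3 both arms follow the same exergame programme at the same volume, within inpatient rehabilitation.

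**The concern.** The three ANOVA effects answer different questions, and only the interaction compares what the two surfaces add. The time effect pools spontaneous recovery, usual rehabilitation and the shared exergame programme. The group effect averages the T1 and T2 values, so half of it is measured before any training. Within-arm changes have the same content as the time effect, one arm at a time. The plan nevertheless treats all three effects alike as triggers and works out its effect sizes within arms.

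The T1 value enters only as a repeated outcome, not as a covariate. The Discussion says that "the study population (persons in the early-subacute phase) is extremely heterogeneous", so baseline differences between two groups of 15 are likely to matter.

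At stake is what is carried forward. According to the Discussion, "if found effective, this study would be the foundation for a larger study that is powered to detect effects". That decision needs a between-arm estimate that is as precise as the data allow.

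**Working it through.** **Inputs.** From section 2.2: 15 per arm, and a later main trial with 90% power at two-sided 5% for a medium effect. The 15 comes from a cited recommendation whose rule the article does not reproduce, so it cannot be recomputed and is taken as given. Assumptions, because the article gives no figures: a medium effect is 0.5 SD; the pre-post correlation ρ is 0.5, 0.7 or 0.9; the recovery shared by both arms is 0 to 0.8 SD. The simulations use 40,000 trials per scenario, 15 per arm, normal data and equal SDs.

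**Step 1: is the interaction valid?** The interaction contrast is (T2 − T1 in the labile arm) − (T2 − T1 in the stable arm). A shift common to both arms cancels. Its F-test is the square of the two-sample t-test on change scores, with 28 degrees of freedom. With no arm difference it rejected in about 5% of simulated trials at every recovery size tried.

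**Step 2: precision.** Per-patient variance in units of SD² is 2(1−ρ) for the change score and 1−ρ² for ANCOVA, so the ratio is (1+ρ)/2. Main-trial size per arm is 2(1.960+1.282)²V/0.5² = 84.1V, rounded up. The last column is simulated power at 15 per arm for a true 0.5 SD difference, using t-tests that already charge ANCOVA its lost degree of freedom.

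| ρ | V, change score | V, ANCOVA | Ratio | Main-trial n per arm | Pilot power |
|---|---|---|---|---|---|
| 0.5 | 1.00 | 0.75 | 0.75 | 85 → 64 | 26.1% → 32.0% |
| 0.7 | 0.60 | 0.51 | 0.85 | 51 → 43 | 40.4% → 44.5% |
| 0.9 | 0.20 | 0.19 | 0.95 | 17 → 16 | 84.1% → 84.4% |

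**Step 3: chance imbalance.** The standard error of the baseline difference between arms is √(2/15) = 0.365 SD. Given a baseline difference Δ, the expected change-score contrast moves by −(1−ρ)Δ. For Δ of one standard error the shift is 0.5 × 0.365 = 0.18 SD, 0.3 × 0.365 = 0.11 SD and 0.1 × 0.365 = 0.04 SD at the three correlations. Regression on T1 removes this shift in expectation when the relation is linear.

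**Step 4: the post-hoc gate and the within-arm effect sizes.** For a true post-training difference δ, the group main effect has expectation (0 + δ)/2 = δ/2. Its simulated power at δ = 0.5 SD is 11% to 12%. With 0.5 SD of shared recovery and no arm difference:

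| Share of simulated trials | ρ = 0.5 | ρ = 0.7 | ρ = 0.9 |
|---|---|---|---|
| Interaction significant | 5% | 5% | 5% |
| Post-hoc gate opens | 78% | 93% | 100% |
| Labile arm significant pre to post | 44% | 64% | 98% |
| Labile arm r at least 0.5 | 43% | 64% | 98% |
| Labile arm significant, stable arm not | 25% | 23% | 2% |

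With 0.3 SD of shared recovery the gate opens in 42%, 58% and 95%. With none it opens in about 14%, because three tests are each run at 5%.

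**The case against.** The strongest reply is that the planned model already contains the right test. This stands. The interaction removes common recovery and holds its 5% error rate. A reader might infer from the trigger and the within-arm effect sizes that the plan credits shared recovery to the labile surface, but no section says that a time effect or a within-arm change will be read as efficacy. The hypothesis is comparative, and the Discussion cites time-by-group interactions when it describes earlier studies. The text leaves that misreading open; it does not commit to it.

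A reader might also infer that baseline is ignored or that the comparison is biased. Neither follows. T1 is used as the pre-training level of the repeated factor, and under randomisation the change-score contrast is unbiased on average. The loss is in precision and in sensitivity to the imbalance that happens to occur.

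Nor can it be said that the pilot will fail to supply figures for a main trial. Section 2.4.4 promises SDs and effect sizes for all outcomes, and further detail may sit in a fuller document.

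Finally, these are secondary outcomes. The feasibility decision in section 2.4.1 rests on adverse events, attrition and adherence, and the Discussion leaves powered testing of effects to a larger study. That limits the weight of the point. It does not answer why a main effect that cannot bear on the hypothesis should open further testing, or why T1 should not be a covariate when it is already measured.

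**Conclusion.** The point holds as an avoidable weakness in the secondary analysis, not as an invalid test. Two things are established from the text: the interaction is a change-score comparison with no baseline covariate, and both the post-hoc trigger and the only described effect-size method reach beyond the between-arm question.

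The precision gain depends on ρ. The variance falls by 25%, 15% or 5% at correlations of 0.5, 0.7 and 0.9, and at 0.9 the gain in pilot power is negligible. The gate and within-arm percentages depend on the assumed recovery and ρ and illustrate the mechanism; they do not predict this trial's results. What does not depend on those assumptions is that the time effect and within-arm changes respond to anything shared by the arms, and that the group main effect carries only half of any post-training difference.

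**What to change.** In section 2.4.4, for each outcome measured at T1 and T2:

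1. Fit T2 = group + T1 and name the group coefficient as the efficacy estimate.
2. Report that adjusted between-arm difference with its 95% CI, and a between-arm effect size.
3. Delete the trigger that lets a group or time main effect open post-hoc tests.
4. Keep within-arm change as description only.

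The planned repeat analysis controlling for length of stay can be run on the same model. The cost is one degree of freedom per model (27 instead of 28 with 15 per arm) and a few lines of wording. All T1 values are already collected, and no assessment, sample size or feasibility criterion changes.

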There is currently just one study that has looked into the effects of exergame-based cognitive-motor training with the additional proprioceptive stimulation by playing the exergames on a labile platform (23). They found that compared to the training on a stable platform and to a passive control group, training on an instable platform is more effective for the improvement of reactive balance and functional mobility under dual-task conditions in healthy, community-dwelling older adults. The feasibility and effects of this type of exergame training on labile surface and thus rich in proprioceptive stimulation in stroke patients remains unknown.

Therefore, the aim of this study is to assess the feasibility and effects of exergame-based cognitive-motor training on a labile platform on physical and cognitive functioning in stroke inpatients.

We hypothesize that exergame-based cognitive-motor on a labile surface will be feasible within the context of inpatient rehabilitation of stroke patients. In addition, we hypothesize that compared to training on stable surface, training on a labile platform will be more effective for the improvement of motor and cognitive functioning in stroke inpatients.

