### Study design and procedures

2.1

The study is a pilot randomized control trial with two parallel groups; a control group and an intervention group with a 1:1 allocation ratio. The study will only be blinded on pre-measurement. Afterward group assignment blinding is no longer possible because the pre-assessments and training sessions will be carried out by the same study staff. Data collection will be carried out in the neurologic rehabilitation clinic in Zihlschlacht, Switzerland. All study procedures will be performed in accordance with the Declaration of Helsinki. The study protocol was reviewed and approved by the Cantonal Ethics Committee of Eastern Switzerland (EKOS 24/002). Any substantial amendment to the study protocol will have to be approved by the same Ethics Committees and the trial registration at clinicaltrials.gov NCT06296069 will be updated accordingly.

At clinic admission, patients potentially fulfilling the eligibility criteria will be informed in oral and written form about the study and asked if they wish to participate. All interested participants will then be screened for eligibility by the local principal investigator. The included participants will undergo the baseline assessments (T1) and will be subsequently randomly allocated to the intervention or the control group using permuted block randomization with blocks of four. Screening and baseline measurements will be conducted within the first two days upon admission. To minimize physical and cognitive fatigue, a consistent assessment sequence alternating between physical and cognitive tests will be enforced. Participants will be encouraged to ask for a break whenever needed. One day after the T1 measurements, the intervention period will begin. The intervention period will be equal to the length of the stay in the rehabilitation clinic (between 3–4 weeks, according to cantonal/regional regulations and insurance coverage). At the last two days before discharge, post-measurements (T2-measurements) will be performed with all (intervention & control) study participants. Participants will be withdrawn from the study if they develop symptoms or diseases regarded as exclusion criteria during the study.

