### Participants and eligibility

2.2

Primary outcomes of this pilot study are feasibility measures (e.g., adherence, attrition, motivation, enjoyment, adverse events) which do not require an *a priori* sample size calculation. The selected sample size is based on the recommendations of Whitehead et al. (25). Since we are aiming for a future main trial designed with 90% power and two-sided 5% significance and aim to be able to detect medium effect sizes, we will use a sample size of n = 15 per treatment arm. Therefore, 30 participants will be included in the study with 15 participants allocated to each group (intervention or control group). Inclusion criteria are: prescription for inpatient rehabilitation due to a stroke, ability to provide a signed informed consent, age ≥ 50 years, Mini Mental State Examination (MMSE) ≥ 20, ability to stand for at least 3 min without external support. Exclusion criteria are: depending on assistance for ambulation (Functional Ambulation Categories <2), insufficient knowledge of the German language to understand the instructions and games, conservatively treated osteoporotic fractures in the last 16 weeks and presence of any mobility, cognitive, sensory and/or psychiatric limitations or comorbidities which impair the ability to play the exergames and/or conduct the pre-/post assessments.

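### The named non-parametric fallback, Friedman's ANOVA, has no group factor, so it cannot compare labile with stable training on secondary outcomes that fail an assumption check

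*Protocol article*

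**What the plan says.** The Introduction (section 1) states a comparative hypothesis: "compared to training on stable surface, training on a labile platform will be more effective" for motor and cognitive functioning. The design has two parallel arms, and "30 participants will be included in the study with 15 participants allocated to each group".

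Section 2.4.4 (Statistical analyses) tests the pre-post physical and cognitive outcomes with a two-way ANOVA, with group as the between-subject factor and time (pre, post) as the within-subject factor. Normality is checked by Shapiro-Wilk and Q-Q plots, and equality of variances by Levene's test. Then: "If any of the assumptions for parametric testing is not met, the non-parametric alternative (Friedman’s ANOVA) will be used". The next step reads: "If the two-way mixed ANOVA or Friedman’s ANOVA report a significant group, time or interaction effect", after which unspecified post-hoc tests follow. The only other rank test named is the Wilcoxon signed rank test, for differences within a group. The significance level is 0.05.

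**The concern.** In the mixed ANOVA, the group-by-time interaction is the term that answers whether labile training does better than stable training. The fallback should keep that term, and Friedman's test does not. It ranks each participant's own measurements against each other and never uses the arm to which the participant belongs.

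The text thus credits a named test with two results that it cannot give. The risk is in interpretation. Both arms receive inpatient rehabilitation with the same exergame programme, so improvement in both is plausible. A significant Friedman result would then show that patients changed during their stay, yet the plan invites the reader to take it as a group or interaction effect. The Discussion (section 4) makes a larger study depend on the training being found effective, so such a misreading could carry forward.

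**Working it through.** The plan gives no figure to reproduce, because the question is one of test structure.

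**Inputs from the protocol article.** Two arms of 15 (section 2.2), two time points, significance level 0.05 (section 2.4.4).

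**Assumed inputs.** Normal data with SD 1 at each time, pre-post correlation 0.6, no ties, and all 30 participants analysed.

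**Step 1: what Friedman's test becomes with two time points.** Let n be the number of participants and s the number whose post value exceeds the pre value. The rank sums are R1 = 2s + (n − s) and R2 = s + 2(n − s). The statistic is

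Q = 12/(n·2·3) × (R1² + R2²) − 3·n·3 = (2s − n)²/n.

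Only n and s enter. The arm does not appear, so there can be no group or interaction term. As a numerical check, group labels were reassigned at random 1,000 times in a sample of 30. The Friedman p-value took 1 distinct value, while the p-value of a Mann-Whitney test on change took 66.

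**Step 2: rejection rule.** With n = 30 and a chi-square limit of 3.84 (1 df), s = 20 gives Q = 10²/30 = 3.33 (not significant) and s = 21 gives Q = 12²/30 = 4.80 (significant). The test rejects when s ≥ 21 or s ≤ 9. With no change in either arm this has probability 0.043.

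**Step 3: both arms improve equally, so the surfaces do not differ.** The SD of the change is √(2 × (1 − 0.6)) = 0.894.

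- Improvement of 0.5 SD: P(post > pre) = Φ(0.5/0.894) = Φ(0.559) = 0.712. With s binomial (30, 0.712), P(s ≥ 21) = 0.644.
- Improvement of 0.8 SD: P(post > pre) = Φ(0.894) = 0.814, and P(s ≥ 21) = 0.961.

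Simulation gives matching results:

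| True state | Friedman significant | Mann-Whitney on change significant |
|---|---|---|
| Both arms +0.5 SD | 64-65% | 4-5% |
| Both arms +0.8 SD | 96% | about 4% |

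The Mann-Whitney rate stays near its nominal 5%, as it should when the arms do not differ.

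**Step 4: skewed data.** With log-normal change scores (log-SD 0.6, assumed; shifts in SDs of the change; 4,000 runs), an equal shift of 0.8 SD in both arms gives 100% for Friedman and 4.5% for Mann-Whitney. The conclusion does not depend on normality.

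**Step 5: how often the fallback would apply.** The article does not say whether normality is checked in each group-by-time cell or on change scores. With normal data and independent 5% checks, two checks (change scores, one per arm) give 1 − 0.95² = 0.098. Four cells give 1 − 0.95⁴ = 0.185, or about 24-27% in simulation with Levene's test added. With log-normal data (sigma 0.5, assumed) the cell-wise rate is about 83-86%. The range is therefore roughly 10% to 86% of outcomes.

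**The case against.** Four points can be made for the plan.

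1. **The primary outcome is feasibility.** The decision rule at the end of section 2.4.1.8 uses adverse events, attrition and adherence. None of these passes through this test, and the Discussion leaves powered effect testing to a larger study. This stands, and it limits the severity.

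2. **Post-hoc tests and effect sizes are promised.** A reader might infer that, for outcomes that switch, the arms would never be compared. The documents do not support that. The post-hoc tests are unspecified and could include a comparison between arms. If only one arm improves by 0.8 SD, Friedman's test is significant in about 72% of the skewed-data simulations, so that step would often be reached. But it is reached because of pooled change over time, and no between-group rank test is named. The provision softens the error without repairing it.

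3. **The fallback may be rare.** A reader might infer that it will be used often. That is not established. The rate depends on where the checks are made, on skew that the article does not quantify, and on judgement of the Q-Q plots.

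4. **Opposite movements are an extreme case.** If the arms moved by +0.5 and −0.5 SD, Friedman's test would reject in about 3% of trials and Mann-Whitney on change in about 80%. Nothing in the article suggests that either arm will decline, so the point should not rest on this scenario.

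An unseen analysis plan does not answer the concern. The article names a test and describes output that the test does not have, which is a stated error and not an omitted detail.

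**Conclusion.** The concern holds for the secondary physical and cognitive outcomes that fail an assumption check. For these, the named omnibus test does not address the labile-versus-stable hypothesis, and the text wrongly credits it with group and interaction effects. This structural conclusion needs no assumption about the data.

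The size does. With 15 per arm, normal data and correlation 0.6, equal improvement of 0.5 SD in both arms makes Friedman's test significant in about 65% of trials although the surfaces do not differ. The analysed number may be below 30, because these analyses are restricted to participants with at least 70% adherence, and the rates would shift accordingly. The share of outcomes affected is unknown.

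Outcomes that pass the checks keep the mixed ANOVA, and the feasibility decision is untouched. This should be fixed, but it does not threaten the primary result.

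**What to change.** In section 2.4.4, replace Friedman's ANOVA with one rank-based method, named in advance, that compares the arms. Two suitable choices are:

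- a Mann-Whitney test on the T2 − T1 change, with the Hodges-Lehmann difference and its 95% confidence interval; or
- rank ANCOVA, with the rank of T2 regressed on group and the rank of T1.

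Other rank-based methods that keep the group factor, such as an aligned-rank or ANOVA-type mixed factorial analysis, would also serve. Delete the wording by which Friedman's test reports group or interaction effects, and make the arm comparison the stated test of the hypothesis, not a post-hoc step conditional on a pooled time effect.

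The cost is analysis wording only. No further data or participants are needed.

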###### Leg proprioception

2.4.2.2.6

Leg proprioception will be assessed using the Dynamic Position Test of the ProMeTo-System. In this test, the examiner will move participants joints (extension or flexion) into several positions/angles. Participants will be asked to memorize and replicate exactly the position that the examiner specified without visual control. Three different joints are tested: hip, knee and ankle. The range of motion (ROM) of every joint is measured by moving the joint two times in either full internal rotation and external rotation for the hip or extension and flexion in the knee prior to the onset of the test. In the ankle joint the plantarflexion and dorsiflexion ROM will be measured. Inertial sensors (Shimmer Research Ltd., Dublin, Ireland) provide the angle difference (in degrees) between the position given by the test leader and the position imitated as accurately as possible by the participant. Average angle differences for each joint will be used for further analyses.

Because there are currently no reference values and/or standard error measurement values for this population, this test will be repeated twice before the onset of the intervention (once during the pre-assessment, together with all the rest of the pre-port assessments and once again one day later, just before starting the first training session) in order to calculate its test–retest reliability and assessment error (minimum detectable difference) for this population.

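### The only effect size whose derivation is specified is a within-arm r from a paired test; it mixes size of change with pre-post correlation and does not answer the between-arm question

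*Protocol article*

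**What the plan says.** Section 2.4.4 promises effect sizes for every primary and secondary outcome, but explains how to obtain one only for change within an arm: "To calculate effect sizes of intragroup differences between post- and baseline measurements, a dependent T-test or its non-parametric equivalent" (the Wilcoxon signed rank test) is to be used. The result is read on r benchmarks, small from 0.01, then "medium (r ≥ 0.3), or large (r ≥ 0.5". No formula from t or Z to r is given, and no metric is named for the comparison of arms. The same section sets the test level: "General level of significance used is established as *p* = 0.05". It restricts these analyses to participants with at least 70% adherence.

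Section 2.2 fixes the pilot size, "we will use a sample size of n = 15 per treatment arm", with a later trial in view: a "future main trial designed with 90% power and two-sided 5% significance", with the "aim to be able to detect medium effect sizes". The Introduction states the effectiveness hypothesis as labile against stable surface, that is, between arms.

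**The concern.** A paired test scales the mean change by the SD of individual changes. An r built from it reflects how consistent the change is across participants as well as how big it is. The outcome battery mixes instrumented gait and mobility measures, reaction times, fNIRS signals and confidence questionnaires, so pre-post correlations may well differ between outcomes. Labels could then order outcomes differently from the size of their changes.

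At this sample size the 'large' cut-off also lies close to the 5% significance boundary, so a table of labels would largely repeat the table of p-values.

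Finally, both arms receive exergame training and inpatient rehabilitation. A 'large' change within the intervention arm says nothing about the added value of the labile surface, which is what the hypothesis concerns and what a main trial would need.

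**Working it through.** **Inputs from the protocol.** 15 per arm (2.2), allocation 1:1 (2.1), level 0.05 (2.4.4), r cut-offs 0.3 and 0.5 (2.4.4), 10% attrition acceptable (2.4.1.2). The stated total agrees: 2 × 15 = 30. The article gives no critical r or numeric effect size to reproduce.

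**Assumptions.** Two-sided tests, equal pre and post SDs, pre-post correlation ρ between 0.3 and 0.95 (the article gives none), and r = t/√(t² + df) with df = n − 1, or Z/√(n pairs) for Wilcoxon.

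**Step 1: where 'large' falls.** Inverting, t = r√(df/(1 − r²)). For n = 15 and r = 0.5, t = 0.5 × √(14/0.75) = 2.160, p = 0.049. Conversely, p = 0.05 (t = 2.145) gives r = 2.145/√(2.145² + 14) = 0.497. For r = 0.3, t = 0.3 × √(14/0.91) = 1.177, p = 0.26.

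The analysed number may be lower than 15. Attrition of 10% alone would remove 3 of 30, leaving 13 or 14 per arm:

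| Pairs analysed | r at p = 0.05 | p at r = 0.5 |
|---|---|---|
| 15 | 0.497 | 0.049 |
| 14 | 0.514 | 0.058 |
| 13 | 0.532 | 0.069 |
| 12 | 0.553 | 0.082 |
| 11 | 0.576 | 0.098 |

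Wilcoxon with Z/√n at 15 pairs behaves alike: a rank sum of 25 gives exact p = 0.048 and r = 0.513; 26 gives p = 0.055 and r = 0.499. With the variant Z/√(2n), r = 0.5 needs Z = 0.5 × √30 = 2.74, p = 0.006, and the near-coincidence disappears.

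**Step 2: dependence on the correlation.** With d the change in baseline SDs, d_z = d/√(2(1 − ρ)) and r = d_z/√(d_z² + (n − 1)/n). At n = 15:

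| d | ρ = 0.3 | 0.5 | 0.7 | 0.8 | 0.9 | 0.95 |
|---|---|---|---|---|---|---|
| 0.2 | 0.17 | 0.20 | 0.26 | 0.31 | 0.42 | 0.55 |
| 0.3 | 0.25 | 0.30 | 0.37 | 0.44 | 0.57 | 0.70 |
| 0.5 | 0.40 | 0.46 | 0.56 | 0.63 | 0.76 | 0.85 |

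The order can reverse:
- d = 0.3, ρ = 0.9: d_z = 0.3/√0.2 = 0.671, r = 0.671/√(0.450 + 0.933) = 0.57, 'large'.
- d = 0.5, ρ = 0.5: d_z = 0.5, r = 0.5/√(0.250 + 0.933) = 0.46, 'medium'.

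Allowing for sampling error at 15 pairs, a true change of 0.3 SD would be called 'large' in about 19% of samples at ρ = 0.5 and about 67% at ρ = 0.9.

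**Step 3: scale of the main trial.** If 'medium' in 2.2 is taken to be a between-arm difference of 0.5 SD (an assumption), its between-arm r with equal arms is d/√(d² + 4) = 0.5/√4.25 = 0.24. This lies below the 0.3 that 2.4.4 calls medium. The same word therefore need not mean the same thing in the two sections.

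**The case against.** Several points on the other side are sound.

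- **A reader might infer that the label reflects the correlation instead of the size of the change.** It does not. At ρ = 0.7, changes of 0.1, 0.2, 0.3, 0.5 and 0.8 SD give r = 0.13, 0.26, 0.37, 0.56 and 0.73. Both matter.
- **A reader might infer that 'large' is simply another name for p < 0.05.** That needs about 15 analysed pairs and one of two conversions that the article does not state. With fewer pairs some 'large' changes are non-significant; with Z/√(2n) the cut-off is stricter than 5%.
- **Pre-post correlation is not retest reliability.** Over three to four weeks of rehabilitation, the spread of change includes real differences in response, in a population that the Discussion calls very heterogeneous. The documents do not show that labels would rank outcomes by reliability.
- **Nothing says that the r labels will size the main trial.** Means and SDs are also to be reported, and the group-by-time ANOVA tests the comparison of arms. Its effect-size metric may be left to the full plan.
- **Noisy labels are not peculiar to r.** With no true change, 26% of within-arm results at 15 pairs reach |r| ≥ 0.3. A between-arm difference over the baseline SD would reach 0.5 in either direction with no true effect in about 25%, 17% and 8% of simulated trials at ρ = 0.3, 0.5 and 0.7. The choice of standardiser is partly preference.
- **Leg proprioception.** Section 2.4.2.2.6 will derive the "assessment error (minimum detectable difference) for this population". An article need not say how results will be read against it, so this is no defect.

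What stands is that the one derivation the article does fix is within-arm, and that its labels are hard to interpret.

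**Conclusion.** The concern holds in a limited form. The specified effect size combines the size of the change with the pre-post correlation. At about 15 pairs its 'large' label adds little to the p-value (p = 0.049 at r = 0.5; 0.069 with 13 pairs), and it can place a 0.3 SD change (r = 0.57) above a 0.5 SD change (r = 0.46). It neither addresses the between-arm hypothesis nor sits on the scale of a between-arm effect. These figures rest on the assumed conversions, two-sided testing, equal SDs and assumed correlations.

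The stakes are moderate. The labels describe secondary outcomes, and no planned test changes. The feasibility decision in 2.4.1.8 rests on adverse events, attrition and adherence. This is a worthwhile, inexpensive improvement in reporting; it does not invalidate the analysis.

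**What to change.** In 2.4.4, for each pre-post secondary outcome:

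- Report the between-arm difference in change, in original units with a 95% CI, as the main effect estimate.
- Add a between-arm standardised difference with its CI, and name the standardiser, for example the pooled baseline SD with small-sample correction.
- Keep within-arm change as description, in original units with a CI, and drop the small/medium/large r labels for it.

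The cost is a few sentences and a few lines of code; no extra data are needed. Some within-arm changes lose the label 'large', and the intervals will be wide. At 15 per arm and ρ = 0.5 the SD of change equals one baseline SD, so the standard error is √(2/15) = 0.365 and the 95% half-width about 2.048 × 0.365 = 0.75 SD (2.048 being the t quantile on 28 df). That width is itself useful to whoever plans the main trial.
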